### Secondary

1. Time to readmission or death following hospital admission for ECOPD
2. All-cause readmission rates at 90 days and 12 months post discharge
3. All-cause mortality rates at 90 days and 12 months post discharge
4. COPD exacerbation rates, from health records and self-reported, at 90 days and 12 months.
5. Rates of adverse cardiovascular events\* at 90 days and 12 months post discharge
6. Rate of new diagnosis of cardiovascular disease at 90 days and 12 months
7. Rate of undertreated cardiovascular disease at baseline, 90 days and 12 months
8. Change in 4 metre gait speed at 90 days and 12 months, compared to baseline
9. Mean change in quality of life measured by St. Georges' Respiratory Questionnaire over 12 months.
10. Health costs and estimated Quality Adjusted Life Years (QALY), measured by health records and patient-completed resource utilisation proforma, at 12 months

In the intervention arm we will also report as secondary outcomes:

11. Changes in right heart function† between baseline and 90 days
12. Relationship between changes in right heart function† and ECOPD severity measured using DECAF score
13. Relationship between changes in right heart function† and comorbid CVD
14. Relationship between right heart function† and COPD severity at baseline.
15. The associations between the primary outcome and right heart function at baselinet.

\* nonfatal stroke or myocardial infarction, and cardiovascular death; † Estimated pulmonary artery systolic pressure (PASP) and tricuspid annular plane systolic excursion (TAPSE) measured by echocardiography.

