### Schedule of Activities

All patients will have the following assessments (conducted face to face unless specified):

|                                   | Baseline | 90 (+/- 10) days † | 6 months (+/- 10 days) - telephone | 9 months (+/- 10 days) - telephone | 12 months (+/- 10 days) |
|-----------------------------------|----------|-------------------------------|------------------------------------|------------------------------------|-------------------------|
| Demographics, comorbidity         | X        | X                             |                                    |                                    | X                       |
| Medications                       | X        | X                             | X                                  | X                                  | X                       |
| eMRCD                             | X        | X                             |                                    |                                    | X                       |
| Spirometry & inspiratory capacity | X        | X                             |                                    |                                    |                         |
| NYHA class                        | X        | X                             |                                    |                                    |                         |
| Rockwood clinical frailty scale   | X        |                               |                                    |                                    |                         |
| COPD assessment*                  | X        |                               |                                    |                                    |                         |
| Bedside observations α | X        |                               |                                    |                                    |                         |
| ABG                               | X        |                               |                                    |                                    |                         |

|                                                  |   |   |   |   |   |
|--------------------------------------------------|---|---|---|---|---|
| ECG                                              | X |   |   |   |   |
| Laboratory tests β                    | X |   |   |   |   |
| 4m gait speed                                    | X | X |   |   | X |

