| SGRQ-C                                           | X | X |   |   | X |
| EQ-5D-5L                                         | X | X |   |   | X |
| Exacerbation frequency                           | X | X | X | X | X |
| Hospital admissions / ED attendances             |   | X |   |   | X |
| Primary & community NHS care visits π |   | X | X | X | X |
| Mortality                                        |   |   |   |   | X |
| Adverse Cardiovascular Events ‡                  |   | X |   |   | X |

† - at clinical stability, defined as > 6 weeks after completion of primary treatment course for COPD exacerbation; \* - includes; BMI, previous spirometry, previous exacerbation / hospital admission / NIV episodes, α- components of NEWS2 scale; π – health service utilisation form; β – full blood count, urea & electrolytes, liver function tests, glucose, albumin, lactate, CRP; ‡ nonfatal stroke or myocardial infarction, and cardiovascular death

In addition to face to face assessments, all patients will be contacted by telephone at 6 and 9 months to complete an assessment of healthcare resource use. In hospital and at 3, 6 and 9 months following hospital discharge, patients will be provided with a health service utilisation form and asked to use this to record all contact with community NHS services. This data will be reviewed with the patient at the face to face (3 and 12 months) and telephone (6 and 9 months) assessments. Data regarding frequency of COPD exacerbations will be collected at these time points; severe exacerbations (requiring admission) will be captured from health records, moderate exacerbations (requiring treatment with antibiotics and/or steroids) will be self-reported.

Clinical stability is required at the 90-day review for accurate assessment of spirometry and, for those randomised to structured cardiovascular assessment, for echocardiography. The 90-day review appointment will therefore be delayed, if necessary, until participants are in a period of clinical stability, which is defined as more than 4 weeks after completion of a course of steroids and/or antibiotics for a diagnosed COPD exacerbation. The research fellow may clinically assess participants to determine if a COPD exacerbation should be diagnosed if a patient is unwell around the time of review. To avoid excessive delay in cases

of recurrent exacerbation, 90 day review will be conducted after the delay has reached 8 weeks, regardless of the recency of exacerbation.

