Those randomised to the structured cardiovascular assessment will also undergo:

|                                                     | Baseline       | 90 days | β – troponin T, NT pro-BNP, fibrinogen, cholesterol profile (admission only), HbA1c (admission only); γ - performed at any point during index hospital admission (or within 7 days of admission); ☉ - performed in patients hypertensive during initial hospital stay, without a prior hypertension diagnosis |
|-----------------------------------------------------|----------------|---------|---------------------------------------------------------------------------------------------------------------------------------------------------------------------------------------------------------------------------------------------------------------------------------------------------------------|
| ECG                                                 | X              | X       |                                                                                                                                                                                                                                                                                                               |
| Echocardiogram                                      | X              | X       |                                                                                                                                                                                                                                                                                                               |
| Laboratory investigations β              | X              | X       |                                                                                                                                                                                                                                                                                                               |
| 24 hour cardiac monitor                             | X              |         |                                                                                                                                                                                                                                                                                                               |

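### Adverse cardiovascular events are reported in both arms, but only the intervention arm has scheduled cardiac tests at 90 days, leaving MI and cardiovascular death open to detection and attribution bias

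*Protocol*

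**What the plan says.** Under Study Endpoints, Secondary, item 5 is "Rates of adverse cardiovascular events\* at 90 days and 12 months post discharge". The event is defined only by a footnote, "nonfatal stroke or myocardial infarction, and cardiovascular death", which also appears under the Schedule of Activities. Outcomes confined to one arm form a separate block (items 11 to 15), introduced by "In the intervention arm we will also report as secondary outcomes". Item 5 stands outside that block, so it belongs to both arms.

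The common schedule opens with "All patients will have the following assessments (conducted face to face unless specified". Its row "Adverse Cardiovascular Events" is marked at 90 days and 12 months. In the same table the ECG is marked at baseline only, and the common laboratory list contains no troponin.

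A second table opens with "Those randomised to the structured cardiovascular assessment will also undergo". It adds an ECG, an echocardiogram and laboratory tests at baseline and again at 90 days. A 24-hour cardiac monitor, a CT calcium score and, for some patients, 24-hour blood pressure monitoring are added at baseline. The laboratory footnote reads "troponin T, NT pro-BNP, fibrinogen, cholesterol profile (admission only), HbA1c (admission only"; the admission-only limit attaches to the cholesterol profile and HbA1c, so troponin T is repeated at 90 days.

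The introduction to Study Endpoints names the hospital administration system as the source for readmission, mortality and length of stay. It names none for MI, stroke or cause of death.

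**The concern.** An event rate can be compared between arms only if an event has the same chance of being recorded in each. Here the schedule makes that chance unequal in two ways.

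- **Detection of nonfatal MI.** At the visit where the first rate is read, intervention patients have a second ECG and echocardiogram to set beside the baseline pair, plus a troponin T. An unrecognised infarct since discharge could come to light. Usual-care patients have no scheduled repeat test. If the 12-month rate is cumulative, an event found this way stays in it, although no extra tests are scheduled at 12 months.
- **Attribution of death.** The baseline search puts more cardiac findings into intervention patients' records. A death with breathlessness in a patient with COPD may more readily be called cardiac when such a finding is on file.

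Both run against the intervention: better detection could look like worse outcome, or a real reduction could be hidden.

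**Working it through.** The protocol states no event rate, effect or test for item 5, so there is no figure to reproduce. The check has two parts.

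**1. Schedule side by side**

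| | Usual care | Intervention |
|---|---|---|
| Item 5 recorded | 90 days, 12 months | 90 days, 12 months |
| ECG | baseline | baseline, 90 days |
| Echocardiogram | none scheduled | baseline, 90 days |
| Troponin T | none scheduled | baseline, 90 days |
| 24-hour cardiac monitor, CT calcium score | none scheduled | baseline |
| Admissions and ED attendances | 90 days, 12 months | 90 days, 12 months |

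The event row is the same in both arms, but the scheduled means of finding an MI are not. The last row is a source common to both arms.

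**2. Scale, under assumptions**

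The documents give 120 patients randomised 1:1, so 60 per arm. The true rates are assumed equal at 5% (60 × 0.05 = 3 events per arm) or 10% (60 × 0.10 = 6). With *k* extra events recorded in the intervention arm only, the apparent risk ratio is (events + *k*) / events.

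| Extra events | 3 per arm | 6 per arm |
|---|---|---|
| 0 | 1.00 | 1.00 |
| 1 | 4/3 = 1.33 | 7/6 = 1.17 |
| 2 | 5/3 = 1.67 | 8/6 = 1.33 |
| 3 | 6/3 = 2.00 | 9/6 = 1.50 |

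With three extra events the chance of a nominally significant excess (two-sided 0.05, normal approximation, rough at these counts) is about 18% at the 5% rate and 13% at the 10% rate. What is at risk is mainly the estimate rather than a false significant result.

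The same effect can be written as observed ratio = true ratio / *s*, where *s* is the share of events that usual care detects relative to the intervention arm. For an assumed *s* of 0.9 to 0.7:

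- true ratio 1.0 appears as 1/0.9 = 1.11 to 1/0.7 = 1.43;
- true ratio 0.7 appears as 0.7/0.9 = 0.78 to 0.7/0.7 = 1.00;
- with *s* = 1 there is no bias.

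For attribution of death, the Scientific Rationale gives one input: among patients without a cardiac history, a quarter had left ventricular dysfunction and 44% had right heart impairment. The rest is assumed: 50–70% of patients without known cardiac disease, 25% of deaths cardiovascular, 25–50% of other deaths in newly labelled patients reattributed, and 12-month mortality of 20–30% (12 to 18 deaths in 60).

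- Low: 0.5 × 0.25 × 0.25 × 0.75 = 0.023 of deaths; 12 × 0.023 = 0.3 extra events.
- High: 0.7 × 0.44 × 0.5 × 0.75 = 0.116 of deaths; 18 × 0.116 = 2.1 extra events.

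This calculation allows usual care no routine new diagnoses, so it leans high. It shows only that an excess between a fraction of an event and about two events is conceivable.

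**The case against.** The strongest reply is that the bias is hypothetical. Nothing says that a finding from the 90-day tests is to be counted as an MI. The review is timed for stability, and the reason given is not a search for infarction: "Clinical stability is required at the 90-day review for accurate assessment of spirometry", with echocardiography named beside it for the intervention arm. One set of tests in a stable patient need not yield an MI diagnosis. A reader might infer that events are in fact over-counted in the intervention arm; the documents support a risk of this and no more.

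Three further inferences also go too far.

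- *That only intervention patients can have new cardiac diagnoses on file.* Cardiovascular treatments leaves usual care to the clinicians in charge, and item 6 counts new diagnoses in both arms. What is peculiar to the intervention arm is the systematic search.
- *That item 5 is the protocol's only measure of harm.* All-cause mortality, all-cause readmission, time to readmission or death, and the primary outcome can all show harm without any cardiac attribution. The protocol does not call item 5 a harm endpoint.
- *That a spurious excess would decide whether a definitive trial follows.* Primary Objective, Limitations and Adaptive design tie that decision, and any extension, to the primary outcome. Outcome measurements names no between-arm test for item 5; the comparison is implied by its place in the list.

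It is also fair that MI criteria and blinded classification commonly sit in an analysis plan or event-review document, so their absence here is no fault. What stands is that the schedule itself creates the unequal testing and the endpoint definition leaves it open. A later document can separate the two kinds of event only if the means of detection was recorded at the time.

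**Conclusion.** The point holds as a risk. Nonfatal MI in item 5 is exposed to detection bias and cardiovascular death to attribution bias, both against the intervention. The stroke component is not directly touched by the extra tests.

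The size cannot be determined from the documents. One extra event would give an apparent risk ratio of about 1.33 from an assumed 3 per arm, or 1.17 from an assumed 6; with equal detection it is 1.00. Every rate behind these figures is an assumption. The consequence is limited to one secondary outcome of a pilot and does not reach the primary outcome. The change is still worth making, because the source of the imbalance is built into the schedule and removing it from the MI component costs almost nothing.

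**What to change.** In the item 5 definition, both under Study Endpoints and in the Schedule of Activities footnote:

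1. In the between-arm comparison, count a nonfatal MI or stroke only if it was diagnosed at a hospital admission or ED attendance after discharge. Both are already collected in all patients.
2. Record how each event was detected. List any event identified solely by the intervention-only 90-day ECG, troponin T or echocardiogram separately and descriptively.
3. Keep cardiovascular death in item 5, state that its attribution may depend on test results available in one arm only, and read it beside all-cause mortality (item 3).
4. If wanted, show all-cause death plus nonfatal MI or stroke as a sensitivity line. It should not replace item 5: with an assumed 12 to 18 deaths and 3 nonfatal events per arm, deaths would make up 12/15 = 80% to 18/21 = 86% of it, so it would largely repeat item 3.

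The cost is a wording change, one recorded field and one or two lines in the results, with no added tests or visits. The small downside is that silent infarcts leave the comparison. Attribution of death is disclosed by this change but not removed as a source of bias.

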## Lay summary

Chronic obstructive pulmonary disease (COPD) is a common lung disease which can flare up and need admission to hospital. Patients with COPD often have heart disease, which worsens their symptoms and increase the chances of death and hospital admission. In the short period after a flare up of COPD, patients are also at a higher risk of heart attacks and irregular heart rhythms, which cause many of deaths and hospital readmissions experienced. Unfortunately, heart disease is often not recognised or not treated adequately in patients with COPD.

We will test whether carefully finding and treating heart disease in patients admitted to hospital with COPD exacerbation is beneficial. 120 patients will take part in this study. 60 patients will be randomly allocated to 'intervention group' and have detailed tests to identify and then treat heart disease. We will compare their outcomes to 60 patients who do not have this assessment.

In all 120 patients, we will record routine clinical information, simple questionnaires and breathing tests. These tests will be repeated 3 and 12 months later. The 60 patients in the intervention group will have detailed heart tests (blood tests, heart scans, and heart monitors). If we find a heart problem we will start treatment. We will compare the two groups to see if patients in the intervention group spend more time living at home during the year after they start the study.

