## Scientific Rationale

This project addresses a healthcare priority. Exacerbations of COPD (ECOPD) are a frequent cause of non-elective hospital admission and are associated with high rates of hospital readmission; 43% of patients were readmitted within 90 days following ECOPD according to the most recent national COPD audit report. Mortality following hospital admission for ECOPD is common, with rates of up to 50% in the most unwell patients during the 12 months following admission. Cardiovascular disease (CVD) is common in COPD and is associated with worse quality of life, and higher mortality and readmission rates [1]. The risks of myocardial infarction and hospital admission for atrial fibrillation (AF) are substantially higher than baseline risk during the short period after hospital admission for ECOPD [2,3].

Despite these known risks, CVD is often undertreated and / or not recognised. Three months after ECOPD requiring hospital admission, a quarter of patients with no past history of cardiac disease have left ventricular (LV) dysfunction and 44% have right heart impairment [4]. In patients with COPD attending pulmonary rehabilitation, 16.5% of patients had impaired LV function (previously undiagnosed in 36%) and 20% had pulmonary hypertension (undiagnosed in two thirds) [5]. There are fewer studies investigating rates of CVD and cardiac dysfunction in patients at the time of ECOPD. Many studies rely on ICD coding diagnoses to define CVD and few clarify the presence of undiagnosed CVD. Marcun et al [6,7] performed echocardiography on 127 patients admitted with ECOPD. An abnormality of left ventricular function was identified in 55% of patients and prevalence of heart failure with reduced (HFrEF) and preserved (HFpEF) ejection fraction was 9% and 19% respectively. A subsequent study of 154 patients from the same group [8] reported 10% of patients had HFrEF and diastolic dysfunction was present in over 50%. These studies did not report on treatment or whether abnormalities had been previously recognised. AF has been reported to be present in between 17% and 35%, [9,10] with rates higher in more severe ECOPD, but the proportion of patients with new AF is unknown.

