## Study Design and Methods

### Methods

A randomised (1:1) pilot study of 120 consecutive consenting patients. The intervention group will undergo a comprehensive cardiac assessment and standardised treatment protocols will be followed to treat identified CVD. Patients will be followed for 12 months to gather outcome data. CVD is defined as hypertension, ischaemic heart disease (IHD), HFPEF, HFREF, atrial or ventricular arrhythmia, moderate-severe valvular heart disease or cor pulmonale.

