### Outcome measurements

Changes in the primary outcome between the intervention and usual care groups will be assessed using Student's t-test or Mann-Whitney U test. Time to first event (readmission or death) will be assessed using a Cox proportional hazards regression model. Changes in echocardiographic measurements between two time points will be assessed using paired Student's t-test or Wilcoxon signed-rank test. The relationship between undiagnosed / undertreated cardiac disease and outcome will be examined using logistic regression. In those surviving to the first follow up assessment, correlations between changes in right heart function and measures of COPD severity and exacerbation severity will be examined using bivariate comparisons appropriate to variable distribution. Mean change in QoL will be calculated by area under the curve per unit time; Student's t-test or Mann Whitney U will be used to compare this value between study arms.

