## Section S2: Management summaries

### SCATECOPD Management summary: heart failure

#### Definitions

*The following practical definitions reflect implementation of evidence and international guidelines by local cardiology services:*

1. Heart failure with moderate-severe LV systolic impairment
  - LVEF < 45% at transthoracic echocardiography (echo)
2. Heart failure without moderate-severe LV systolic impairment
  - LVEF ≥ 45% with echo report of LV diastolic dysfunction
3. Right sided heart failure:
  - Echo evidence of RV impairment in patient with peripheral oedema

*Echo should be performed as early as possible during admission. If NIV used, wait until weaned to periods of ≥ 4 hours off NIV*

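### Undertreated CVD is listed as an outcome for both arms, but most of the tests that reveal CVD are scheduled only in the intervention arm, so rates by arm and a pooled logistic model mix ascertainment with allocation

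*Protocol*

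**What the plan says.** The Protocol's general list of secondary outcomes includes item 6, "Rate of new diagnosis of cardiovascular disease at 90 days and 12 months", and item 7, "Rate of undertreated cardiovascular disease at baseline, 90 days and 12 months". Items 11 to 15 follow under a separate lead-in that confines them to the intervention arm; items 6 and 7 come before it. In the Objectives section, the first secondary objective (rates of undiagnosed or undertreated CVD) names no arm, whereas the third, on cardiac function, is confined to the intervention group.

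The testing schedule differs by arm. Under Schedule of Activities, "Those randomised to the structured cardiovascular assessment will also undergo" introduces a repeat ECG, echocardiography, troponin T, NT-proBNP and other bloods, a 24 hour cardiac monitor, CT calcium scoring and, for selected patients, 24 hour blood pressure monitoring. The Lay summary says of usual care: "We will compare their outcomes to 60 patients who do not have this assessment". All participants have a baseline ECG, bedside observations, routine bloods, NYHA class, and comorbidity and medication history.

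Under Outcome measurements, "The relationship between undiagnosed / undertreated cardiac disease and outcome will be examined using logistic regression". No arm is named.

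**The concern.** The Protocol defines CVD to include both types of heart failure, arrhythmia, moderate to severe valve disease and cor pulmonale. Most of these need a test that usual care is not scheduled to have. Disease that nobody has looked for cannot be recorded as undertreated, so usual care may appear better treated simply because it was examined less.

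The baseline rate shows this most clearly. Before any treatment effect is possible, the true rates are equal in expectation, yet the recorded rates could differ.

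The logistic model has a related problem. Undiagnosed disease can be found systematically in only one arm, where it is then treated. In a pooled model, the recorded exposure partly stands for allocation. These figures serve the first secondary objective and, according to Study Endpoints, help to power the definitive trial.

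**Working it through.** The Protocol gives no expected rate for these outcomes and no power calculation, so there is no stated figure to reproduce. What follows illustrates size only.

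**Inputs from the Protocol**
- "A randomised (1:1) pilot study of 120 consecutive consenting patients", hence 120 / 2 = 60 per arm, which agrees with the Lay summary.
- Hidden-disease rate p = 25%. Scientific Rationale reports LV dysfunction in a quarter of patients without cardiac history, three months after a hospital-treated exacerbation.
- A lower alternative from the same section, in a pulmonary rehabilitation population: 16.5% with impaired LV function, undiagnosed in 36% of them, so 0.165 × 0.36 = 5.9% of all patients.

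**Assumptions**
- The 25% applies at baseline, equally in both arms, to participants without known CVD (those at risk).
- The intervention arm finds every case, and each counts as undertreated.
- Usual care finds a share s, taken from 0 to 0.75.

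**Spurious gap among those at risk:** p − p × s = p × (1 − s).

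| s | Intervention | Usual care | Gap (points) |
|---|---|---|---|
| 0 | 25% | 0% | 25 |
| 0.25 | 25% | 6.3% | 18.8 |
| 0.50 | 25% | 12.5% | 12.5 |
| 0.75 | 25% | 18.8% | 6.3 |
| 1 | 25% | 25% | 0 |

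With p = 5.9% the gap is 5.9 points at s = 0 and 1.5 points at s = 0.75. Over a whole arm, the gap shrinks in proportion to the share without known CVD. If that share were half (assumed), 25 to 6.3 points would become 12.5 to 3.1.

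**Logistic model, if the arms are pooled.** Further assumptions: event risk 50% in usual-care patients without hidden disease; undetected usual-care cases coded as unexposed; any treatment effect acting on the whole intervention arm. The share of recorded cases lying in the intervention arm is 1 / (1 + s): 100% at s = 0, 80% at 0.25 and 67% at 0.5.

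Worked example with s = 0, true odds ratio 2 and treatment odds ratio 0.5:
- Recorded as exposed: odds 1 × 2 × 0.5 = 1.
- Recorded as unexposed: weights 0.375, 0.375 and 0.125 with risks 1/3, 1/2 and 2/3. Mean risk (0.125 + 0.1875 + 0.0833) / 0.875 = 0.452, odds 0.826.
- Pooled odds ratio 1 / 0.826 = 1.21.

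The same calculation elsewhere gives:

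| True OR | Treatment OR | s = 0 | s = 0.25 | s = 0.5 | s = 1 |
|---|---|---|---|---|---|
| 2 | 1 | 1.82 | 1.86 | 1.90 | 2.00 |
| 2 | 0.5 | 1.21 | 1.43 | 1.62 | 1.96 |
| 1 | 0.5 | 0.67 | 0.78 | 0.87 | 1.00 |
| 1 | 1 | 1.00 | 1.00 | 1.00 | 1.00 |

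Unequal ascertainment therefore weakens a true association. It creates a false one only when allocation itself affects outcome.

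**The case against.** The strongest reply is that no comparison of items 6 and 7 is written. Outcome measurements names between-arm methods for the primary outcome and quality of life, and a Cox model for time to first event, but none for these rates. The first secondary objective only asks for rates to be reported, and a SAP that is not shown may settle the arms. This largely stands: a reader might infer a planned significance test, and the Protocol contains none. It is only a partial answer, because the synopsis also has an objective that sets the treatment effect on the primary outcome against that on the secondary outcomes. Nor can a SAP recover tests that were never done.

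Item 7 may also mean known disease only. The Protocol names undiagnosed and undertreated as alternatives, and its one explicit definition of undertreatment, for diabetes in Section S2, covers patients already on treatment. On that reading the illustrated baseline gap disappears. The text does not say which reading applies.

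Usual care is not blind to CVD either: it has the baseline ECG, observations and whatever its clinicians order. Zero detection is therefore an extreme. And more new diagnoses under item 6 are largely the intended yield.

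Three stronger readings are tempting but unsupported:
- Scientific Rationale also reports right heart impairment in 44% of patients, and a reader might count all of it as undertreated CVD. The Protocol's CVD definition requires cor pulmonale, and Section S2 requires peripheral oedema as well as RV impairment for right-sided heart failure.
- A reader might infer from "LVEF ≥ 45% with echo report of LV diastolic dysfunction" that HFpEF will be overcounted by the ratio of the background rates of diastolic dysfunction and HFpEF. Those rates come from two different studies, and the Section S2 wording is a practical management definition, not stated to be the endpoint definition.
- A reader might think the logistic model is misapplied to the count of days alive outside hospital. The sentence says only outcome, and binary readmission and mortality outcomes are listed.

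**Conclusion.** The point holds for item 7 and for a pooled logistic model, and to a lesser degree for item 6. The endpoint list and the test schedule do not fit together: outcomes that depend on detection are listed for everyone, while most of the detection is scheduled in one arm.

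The size is conditional. Among participants without known CVD, the artefact at baseline is about 25 to 6 points if the hidden rate is 25%, screen-detected cases count as undertreated, and usual care detects 0 to 75%. It is smaller with a lower hidden rate and over a whole arm, and nil if item 7 covers known disease only. At 90 days and 12 months its direction cannot be fixed, because detected disease is meant to be treated.

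The logistic figures rest on the assumed event risk and odds ratios, and on pooling, which the Protocol neither states nor excludes. The primary outcome is unaffected. This should be corrected, but it does not threaten the trial's main result.

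**What to change.** - **Item 7:** compare undertreatment between arms only in participants with CVD known before admission, which is already a randomisation stratum. Use criteria that can be judged from data collected identically in both arms, such as comorbidity and medication records, and not from intervention-only tests. State whether screen-detected disease counts.
- **Screen-detected or undiagnosed CVD:** report it in the intervention arm only, with a confidence interval.
- **Item 6:** report it by arm as diagnostic yield, not as a difference in disease incidence.
- **Logistic model:** for undiagnosed disease, run it in the intervention arm only, as exploratory, on a binary outcome such as 12-month death or readmission. Note that detected disease is then treated, so the estimate is not that of untreated disease. For example, if treatment halved the odds only in those detected, a true odds ratio of 2 would show as 2 × 0.5 = 1.

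The change is to wording in the endpoint and analysis sections, with no new data. The cost is precision: fewer patients enter the undertreatment comparison, and at most 60 enter the model. If half of the intervention arm (30, assumed) had no known CVD, a 25% rate of screen-detected disease would carry a 95% interval of about ± 1.96 × √(0.25 × 0.75 / 30) = ± 15.5 points.
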